#### Cross-sectional analysis of effectiveness of the RHIVA2 implementation programme in Hackney, a sexual health NIS in Tower Hamlets and usual care in Newham

We will examine the impact of the sexual health NIS on the serology testing rate in all Tower Hamlets practices (comparing testing rates preimplementation and postimplementation). We will repeat this analysis but also including practices in Newham, which received no intervention at any stage, to act as a comparator. The date of intervention will be defined as the date when the sexual health NIS system went live for all practices (April 2011). We will also compare the RHIVA2 implementation in Hackney with the introduction of the sexual health NIS in Tower Hamlets.

We will conduct similar analysis to the above, with the endpoint of HIV diagnosis, rather than testing.

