#### Coprimary outcome measures

Rates of HIV testing (combined rapid and serology testing; number of patients tested/1000 population/year)Rates of new HIV diagnosis (number of newly diagnosed patients/10 000/year)

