#### Secondary outcome measures

Secondary outcome measures will include data on type of HIV test (serology; rapid), location of diagnosis, stage of disease and linkage to secondary care and retention in secondary care:Number/rate of patients who received a rapid HIV test.Number/rate of patients who received a serology HIV test.Number/rate of patients newly diagnosed in general practice.Mean and median CD4 count of patients newly diagnosed in primary care.Proportion of patients with a CD4 count <350 cells/μL of blood.Proportion of patients with a CD4 count <200 cells/μL of blood.Proportion of patients newly diagnosed with HIV in primary care who attend an HIV specialist department within 1 week of diagnosis.Proportion of patients newly diagnosed with HIV in primary care who attend an HIV specialist department within 2 weeks of diagnosis (BHIVA Standards of Care for people living with HIV (PLHIV), Standard 2, 2013).^25^Proportion of patients newly diagnosed with HIV in primary care who attend an HIV specialist department within 4 weeks of diagnosis (NHS England Standard).Proportion of patients newly diagnosed with HIV in primary care who attend a HIV specialist department within 3 months of diagnosis (Optimising testing and linkage to care for HIV across Europe, OptTEST, 2013).Number of patients previously known to have HIV, who attend an HIV specialist clinic between 12 and 24 months following new diagnosis in primary care (BHIVA Standards of Care for PLHIV, Standard 2, 2013).

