#### Longitudinal analysis of effectiveness of RHIVA2 implementation programme in Hackney

We will compare testing rates using an ITS regression approach with a mixed Poisson model (or negative binomial model if there is overdispersion) to analyse the effect of interventions. Mixed Poisson regression will allow for the clustered nature of the data, that is, allowing each practice to have a different intercept (baseline HIV testing rate). We will also adjust for practice list size as an offset variable in the analysis. Using this approach, it will be possible to examine whether there is a change in level and/or a change in regression slope following the implementation of the intervention.

We will first examine the impact of the RHIVA2 intervention on combined serology and rapid HIV testing rate in practices that received the RHIVA2 implementation (post-trial setting, comparing testing rates preintervention and postintervention). We will repeat this analysis including practices which did not receive the RHIVA2 intervention during the trial or the further implementation phase, to act as a comparator. This will allow comparison of testing rates in practices postimplementation to their preimplementation rates, also adjusting for continuing trends in practices that did not receive the RHIVA2 implementation. We will also repeat the analysis using Newham practices (which received no intervention) as a further comparator.

The date of intervention will be defined as the date of the first RHIVA2 training session. We will conduct similar analysis to the above, with the endpoint of HIV diagnosis, rather than testing.

To assess sustainability, we will model testing rates in practices that received the RHIVA2 intervention during the trial period, considering an interaction term between time postintervention and whether practices were retrained. This will allow an assessment to be made about whether retraining influences the slope postintervention, that is, the sustainability of the RHIVA2 intervention.

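### The Tower Hamlets and Tower Hamlets v Newham testing analyses are specified on serology alone, not on the combined-testing coprimary, and the test type for Hackney v Tower Hamlets is not stated

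*Protocol article*

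**What the plan says.** All references are to the protocol article.

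- **Coprimary outcome measures** defines the testing outcome as "Rates of HIV testing (combined rapid and serology testing; number of patients tested/1000 population/year". The other coprimary is "Rates of new HIV diagnosis (number of newly diagnosed patients/10 000/year".
- **Secondary outcome measures** lists, separately, "Number/rate of patients who received a serology HIV test".
- **Longitudinal analysis (Hackney)** uses the combined rate: "We will first examine the impact of the RHIVA2 intervention on combined serology and rapid HIV testing rate in practices that received the RHIVA2 implementation". It then adds: "We will also repeat the analysis using Newham practices (which received no intervention) as a further comparator".
- **Cross-sectional analysis (three boroughs)** names a different rate: "We will examine the impact of the sexual health NIS on the serology testing rate in all Tower Hamlets practices". It continues: "We will repeat this analysis but also including practices in Newham, which received no intervention at any stage, to act as a comparator". The direct borough comparison follows: "We will also compare the RHIVA2 implementation in Hackney with the introduction of the sexual health NIS in Tower Hamlets". The section closes by planning similar analyses with HIV diagnosis as the endpoint.

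The cross-sectional section gives no reason for restricting the testing endpoint to serology.

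**The concern.** The second and third research questions in the Introduction are cross-borough: Hackney against Tower Hamlets, and both against Newham. They can be answered on one scale only if all three boroughs are measured on the same testing outcome. As written, Newham is the comparator on the combined rate for Hackney and on the serology rate for Tower Hamlets, so those two contrasts cannot be set beside each other directly.

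A serology-only rate also leaves out patients whose only test was rapid. The Strengths and limitations box and the Discussion report rapid testing pilots in a few Newham practices. In Hackney, rapid testing is a core part of the programme. If the serology wording were carried into the Hackney v Tower Hamlets comparison, it would remove part of what that programme delivers. The Cost-effectiveness section takes screening uptake from these analyses, so an inconsistent measure of uptake could pass into the three-borough economic comparison.

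**Working it through.** **1. The plan's own figure.** The only number attached to the Tower Hamlets analysis is its count of monthly time points. April 2009 to June 2015 is 75 months. April 2009 to March 2011 gives 24 before the service started, and April 2011 to June 2015 gives 51 from the start onward; 24 + 51 = 75. The stated 24 and 51 reproduce. The issue is the endpoint, not the counts.

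**2. Endpoint by comparison.**

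| Comparison | Section | Testing endpoint as written |
|---|---|---|
| Hackney pre/post | Longitudinal | combined (coprimary) |
| Hackney v Newham | Longitudinal | combined (coprimary) |
| Tower Hamlets pre/post | Cross-sectional | serology only (secondary) |
| Tower Hamlets v Newham | Cross-sectional | serology only, by repetition |
| Hackney v Tower Hamlets | Cross-sectional | not stated |

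**3. Possible size.** The documents give no rapid share, so this step is an illustration on assumed values. Let *q* be the share of tested patients in the comparator borough whose only test was rapid, and let *r* be the same share in Tower Hamlets. Assume equal true combined rates *T*.

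With serology alone in both boroughs, the apparent Tower Hamlets/comparator ratio is *T*(1 − *r*) / [*T*(1 − *q*)] = (1 − *r*)/(1 − *q*). With *r* = 0 it is 1/(1 − *q*):

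| *q* (assumed) | 0% | 5% | 10% | 20% | 30% | 50% |
|---|---|---|---|---|---|---|
| apparent ratio (true value 1.00) | 1.00 | 1.05 | 1.11 | 1.25 | 1.43 | 2.00 |

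These are ratios of levels. The planned model gives each practice its own intercept, which absorbs a rapid share that is constant over time. For a contrast of pre-to-post changes with *r* = 0 throughout, the distortion factor is (1 − *q* before)/(1 − *q* after). It equals 1.00 if the share does not move, and takes the values in the table if the share rises from 0 to *q*.

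**4. Three readings of Hackney v Tower Hamlets.**
- Combined in both boroughs: no distortion from this source.
- Serology in both: the table applies, with *q* the Hackney share.
- Combined in Hackney, serology in Tower Hamlets: the ratio is 1 − *r*, which is 1.00 if Tower Hamlets did no rapid testing.

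The text does not choose among them.

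**The case against.** A reader might infer that the cross-borough comparison as a whole is off the coprimary outcomes. The document does not support that. HIV diagnosis, the other coprimary, is analysed across boroughs in the same section. Hackney v Newham is on the combined rate. For Hackney v Tower Hamlets no test type is named, and the defined coprimary is a natural default. An article may leave such a detail to the full protocol or the analysis plan, so that silence is not an error in itself. Nor does the text say that Hackney's rapid tests will be dropped, or that a combined Hackney rate will be set against a serology rate. These are possible readings, not stated plans.

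The restriction also has a plausible reason. The Interventions section says the Tower Hamlets service pays for HIV testing by serology, and it describes no rapid testing there. If rapid testing was rare, the two rates nearly coincide in that borough. In Newham the only documented rapid testing is a few pilots, which the authors disclose as a limit on comparability. Nothing shows that rapid tests replaced venous samples there.

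All of this stands, and it limits the size of the point. It does not remove the point. The cross-sectional section affirmatively names an endpoint that differs from the coprimary, without a reason. If serology is nearly all testing in Tower Hamlets, using the combined rate there loses nothing. The payment structure in Tower Hamlets is also no reason for a serology-only rate in Newham.

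**Conclusion.** The point holds for two analyses. On the testing endpoint, Tower Hamlets pre/post and Tower Hamlets v Newham are specified on a secondary outcome, while the coprimary and the Hackney analyses use the combined rate. For Hackney v Tower Hamlets the endpoint needs to be stated. The diagnosis coprimary is untouched.

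The numerical effect cannot be fixed from the document. Within Tower Hamlets it may be close to nil. For Tower Hamlets v Newham it is probably towards the low end of the illustrated range, given how limited the pilots were. It could be material for Hackney v Tower Hamlets, but only if serology alone were used there. All illustrated ratios rest on assumed rapid shares, equal true combined rates and no rapid testing in Tower Hamlets. This is an inconsistency that should be corrected; it does not undermine the design.

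**What to change.** In the cross-sectional section, name combined rapid plus serology testing as the coprimary testing endpoint for Tower Hamlets pre/post, Tower Hamlets v Newham and Hackney v Tower Hamlets. Report the serology-only rate in each as the secondary outcome already listed. If the authors prefer to keep serology alone for Tower Hamlets, they should give the reason and show how much rapid testing took place there.

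The cost is mainly wording. The HIV testing data section plans searches on borough-specific codes for both test types, so no new data source is called for. It describes collection still to be done, and it does not confirm that both kinds of code are in use in every borough; that needs checking. One drawback remains: the Discussion warns that data from the Newham rapid pilots may not be accounted for, so the combined Newham rate may still be incomplete. That should be stated as a limitation of the Newham comparisons.

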**Ethics and dissemination:**

The chair of the Camden and Islington NHS Research Ethics Committee, London, has endorsed this programme as an evaluation of routine care. Study results will be published in peer-reviewed journals and reported to commissioners.

Strengths and limitations of this studyThe study will use existing trial data preceding the implementation programme in addition to post-trial data, collected using similar methods to those used in the trial.Fully anonymised general practice data from all participating boroughs will be remotely extracted using a single general practice computer system (Egton Medical Information Systems, EMIS).A large dataset with at least 12 time points before and at least 29 time points after the intervention implementation will provide precise estimation of the effects of intervention using interrupted time series analysis.Differences in HIV testing protocols, data quality and extraction between Hackney, and Tower Hamlets and Newham; and previous interventions such as rapid HIV testing pilots in a small number of Newham practices, may affect comparability between boroughs. Also, cross-contamination of Rapid HIV Assessment 2 (RHIVA2) control practices from intervention practices, or between boroughs, may have occurred.Finally, the post-trial implementation programme of the RHIVA2 intervention differed slightly from the research intervention to account for the complexities of delivering services in routine healthcare settings.

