#### Newham

*Usual care*—no specific borough-wide initiatives were promoted relating to HIV testing in primary care.

The RHIVA2 intervention is based on published clinician behaviour change programmes,^16–18^ and the Tower Hamlets NIS follows Royal College of General Practitioners guidance on establishing general practice federations.^23^ We will report our study in accordance with the STARI reporting guidelines for implementation studies.^24^

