We cannot exclude occurrence of any cluster or crossover effects, although we would expect for this to be minimal given that we detected a more than fourfold increase in HIV testing rates between the RHIVA2 trial intervention and control practices. In contrast to the network structure in Tower Hamlets, Hackney practices, which were randomly allocated to the trial arms, may have informally worked collaboratively through geographical proximity. Due to this potential clustering effect, inference of generalisability of RHIVA2 findings in other boroughs should, therefore, be treated with caution. Furthermore, an audit of new diagnosis and safe coprescribing was also conducted by our team across 31 of the 44 Hackney practices during the implementation phase‚ potentially causing contamination of control practices. However, the number of both trial intervention (n=13) and control (n=15) practices was comparable, suggesting equal exposure to this audit across both arms.^22^ Although public health teams informally collaborate across Northeast London, crossover between boroughs is unlikely given that services are developed and budgeted separately. Our analysis will adjust for any potential contamination using various vertical and horizontal controls both within Hackney, as well as between boroughs using Newham, which has been devoid of any local service HIV promotional intervention, as control.

Moreover, the RHIVA2 trial and post-trial implementation will not be grouped as the same intervention. We will only use the post-trial implementation practices in the main analysis and only consider the trial intervention practices for the assessment of sustainability. Therefore, the sustainability analysis will have to be interpreted with caution with regards to the sustainability of the post-trial intervention, as the intervention in trial conditions might be different to that outside of trial conditions.

We may not be able to account for missing data such as from patients lost to follow-up after diagnosis in general practice, or from rapid testing pilots conducted in a small number of Newham practices during the study period.

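### Newham is analysed as an untreated control, yet the protocol reports rapid-testing pilots in some Newham practices during the study, and no analysis allows for them

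*Protocol article*

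**What the plan says.** Three statements in the protocol article present Newham as untreated:

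- The cross-sectional analysis section repeats the Tower Hamlets analysis with "practices in Newham, which received no intervention at any stage, to act as a comparator".
- The longitudinal analysis section repeats the Hackney analysis "using Newham practices (which received no intervention) as a further comparator".
- The Discussion says that contamination will be adjusted for with several controls, among them "using Newham, which has been devoid of any local service HIV promotional intervention, as control".

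Three other statements differ:

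- The Newham paragraph under Interventions claims less: "no specific borough-wide initiatives were promoted relating to HIV testing in primary care".
- The Discussion lists, among the data that may be missing, those from "rapid testing pilots conducted in a small number of Newham practices during the study period". The sentence opens "We may not be able to account for missing data".
- The strengths and limitations list, after the abstract, names "previous interventions such as rapid HIV testing pilots in a small number of Newham practices" as something that may affect comparability between boroughs.

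Under Organisational data, the team plans to ask in all three boroughs about other activities that promote HIV testing. Neither effectiveness analysis section says how the answers will be used.

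**The concern.** A practice that ran a rapid-testing pilot received a form of the activity under evaluation. If it stays in the control group unmarked, the Newham trend is not purely a usual-care trend, and the contrast with it is biased for the effect of a programme against none. The practice-specific intercept in the mixed Poisson model absorbs stable differences between practices. It does not absorb a pilot that starts or stops partway through the series.

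Most is at stake for Tower Hamlets, where Newham is the only outside control without a programme. For Hackney, Newham comes after the pre/post comparison and the untreated Hackney practices. Newham is also the reference in the third study question. The Discussion relies on it to deal with contamination elsewhere, which is hard to defend if the control is itself affected.

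**Working it through.** **1. Texts side by side.** The cross-sectional section allows no intervention at any time. The Discussion places pilots inside the data window of April 2009 to June 2015. The limitations list itself classes the pilots as interventions. Only the Newham paragraph is compatible with all of this, because a few pilots are not a borough-wide initiative. Timing is also unclear: the limitations list calls the pilots previous, while the Discussion puts them within the study period. The two agree only if previous means before the implementation programme rather than before the study, and the text does not say.

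**2. The plan's own figure.** For Tower Hamlets the sample size section gives 24 monthly points before April 2011 and at least 51 after. April 2009 to March 2011 is 24 months. April 2011 to June 2015 is 9 + 36 + 6 = 51 months. Both figures reproduce. A pilot within the study period therefore falls in the earlier segment, the later one, or both, and the direction of bias depends on which.

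**3. Illustrative size for combined testing.** The document gives no pilot share, pilot effect or pilot dates, so these inputs are assumptions:

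- f, the share of Newham's baseline testing in pilot practices: 2% to 20%.
- r, the rate ratio in those practices while piloting: 1.5 to 4. The upper end borrows the more than fourfold contrast that the Discussion reports between arms of the RHIVA2 trial.
- True relative effect: 1.50.

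Newham's rate is multiplied by 1 + f(r − 1). If all pilot tests are captured and the pilots fill the post period only, the apparent effect is 1.50 / [1 + f(r − 1)]. If they fill the pre period only, it is 1.50 × [1 + f(r − 1)].

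| f | r | Newham multiplied by | 1.50 appears as (post only) | 1.50 appears as (pre only) |
|---|---|---|---|---|
| 2% | 1.5 | 1.01 | 1.49 | 1.52 |
| 5% | 2 | 1.05 | 1.43 | 1.58 |
| 10% | 2 | 1.10 | 1.36 | 1.65 |
| 5% | 4 | 1.15 | 1.30 | 1.73 |
| 10% | 4 | 1.30 | 1.15 | 1.95 |
| 20% | 4 | 1.60 | 0.94 | 2.40 |

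These are ratios of average rates, not the level and slope terms of the planned model. Pilots that covered only part of a segment would do proportionally less.

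**4. Direction by outcome.**

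- *Combined rapid and serology testing (coprimary).* Captured post-period pilot tests raise the control and shrink the effect. Pre-period pilots inflate it. Uncaptured post-period rapid tests that replace serology lower the recorded control rate and also inflate it.
- *Serology testing (the testing outcome named for Tower Hamlets).* Rapid tests do not enter this rate, so the table does not apply. Pilots act only indirectly: substitution lowers Newham serology and raised awareness increases it.
- *New diagnoses (coprimary).* Diagnoses come from clinical HIV service lists and tests from code searches in practice records. A case found in a pilot could therefore be counted even where its test is not.

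**The case against.** The strongest reply is that the authors disclose the pilots twice and plan to collect information on such activities, and that the handling of a few practices belongs in an analysis plan. In addition, no intervention can be read as neither RHIVA2 nor the Tower Hamlets service, and the Discussion's denial is limited to local service promotion. Usual care may legitimately contain small pilots, and the evaluation includes all practices by design.

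Part of this stands. The absence of detailed handling rules would not be a finding on its own. The inclusive design is also a good reason to keep pilot practices in the main comparison: excluding them could remove the more testing-minded practices from the control borough alone. But the narrow reading fits poorly with a statement that covers every stage, and the limitations list itself calls the pilots interventions. Disclosure does not alter the stated analyses, which enter Newham as untreated.

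A reader might go further and infer that the Newham control is shown to be contaminated by, say, 15% or 30%. The document does not support that. Those values need an assumed 5% or 10% share, the effect of the full trial package, and complete capture in the post period only. Nor does it support saying that diagnoses are certainly distorted, because no pilot-found case is reported. Newham is not the main control for Hackney, and only the Discussion dates the pilots to the study period.

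**Conclusion.** The description of the comparator contradicts the protocol's own account of the pilots, and the stated analyses follow the incorrect description. This leaves an unaddressed source of bias, chiefly in the Tower Hamlets comparison and secondarily in the Newham comparison for Hackney. Under the assumed ranges Newham's combined testing rate would be inflated by about 1% to 60%. An assumed true ratio of 1.50 could then appear as anything from 0.94 to 2.40, depending on when the pilots ran. The extremes need a large pilot share together with the trial's full effect. With only a small number of practices mentioned, values nearer the lower end are more plausible, although the document sets no bound. Direction is open. The contradiction in wording does not depend on any of these assumptions.

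**What to change.** 1. In the longitudinal section, the cross-sectional section and the Discussion, describe Newham as the Newham paragraph does: usual care without a borough-wide initiative.
2. Reconcile the two accounts of when the pilots ran.
3. Use the planned collection of organisational data to identify pilot practices and their start and end dates.
4. Keep all Newham practices in the main comparison. For both coprimary outcomes, prespecify a sensitivity analysis that either excludes the pilot practices or marks their pilot periods with a time-varying indicator. Exclusion needs only the practices' identities; the indicator needs dates as well.
5. Report both results, and do not claim that Newham adjusts for contamination unless they agree.

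The cost is a wording change, one flag per practice, one extra analysis per coprimary outcome, and slightly fewer Newham practices in that analysis if exclusion is chosen.
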